## Abstract

**Background:**

Frailty is a clinical state that increases susceptibility to minor stressor events. The risk of frailty is higher in chronic conditions, such as Chronic Obstructive Pulmonary Disease (COPD). Recent studies on COPD have shown that patients living with frailty have an increased risk of mortality. The presence of cardiovascular diseases or conditions are common in COPD and may increase the risk of death.

**Methods:**

This protocol describes a European prospective cohort study of community-based people, in a stable condition with diagnosis of COPD (as defined by GOLD guidelines) across hospitals in Italy and UK. Frailty prevalence will be assessed using the Clinical Frailty Scale. At 1- and 2-year follow up, primary outcome will be the impact of frailty on the number of cardiovascular events; secondary outcomes: the influence of frailty on cardiovascular mortality, all-cause mortality, and deaths due to COPD. For the primary outcome a zero-inflated Poisson regression will compare the number of cardiovascular events at 1 year. Secondary outcomes will be analysed using the time to mortality.

**Discussion:**

This multicentre study will assess the association between frailty and cardiovascular events and mortality in population with COPD. Data collection is prospective and includes routine clinical data. This research will have important implications for the management of patients with COPD to improve their quality of care, and potentially prognosis.

**Trial registration number:**

NCT05922202 (www.clinicaltrials.gov).

## Introduction

Frailty is a clinical syndrome that increases vulnerability to stressors due to decline of multiple physiological reserves. People living with frailty area at higher risk of falls, disability, long hospitalisations, access to care homes, and death [1]. There are two principal approaches of identification of frailty: the deficit accumulation model and the phenotype model [1, 2]. Based on these models, different tools have been created and validated to assess frailty in clinical practice [3].

Chronic diseases such as Chronic Obstructive Pulmonary Disease (COPD) increase the risk of frailty [3, 4]. Literature on frailty in COPD have been emerging in the recent years. While frailty is not synonym for ageing, it is well known that people over 65 years are more likely to live with frailty [4]. In addition, prevalence of COPD increases with age [5]. A double probability of being frail has been demonstrated in patients with COPD compared to patients without COPD in the paper of Marengoni et al. The study reported a prevalence of frailty in COPD between 9% and 64% based on the phenotype model and from 9% to 28% using different frailty assessment instruments [6]. Studies have shown that frailty can increase the risk of mortality in patients with confirmed diagnosis of COPD according to GOLD guidelines (www.goldcopd.org) [7–12].

Cardiovascular diseases share common risk factors with COPD such as ageing, active smoking, and sedentary lifestyle. COPD and CVD frequently co-exist and are associated with worse outcomes than either condition alone. Additionally, the risk of cardiovascular events is higher after COPD exacerbation [13, 14]. Cardiovascular comorbidities are very common in patients with COPD and can increase the risk of death in this population [5, 15, 16].

The present protocol describes a research study project on patients with COPD to investigate the influence that frailty can have on the risk of cardiovascular events in these patients. The project will assess the association between frailty and cardiovascular mortality, and the relationship between frailty and all-cause mortality and COPD-related mortality. Our team have widely collected data on frailty previously using routinely collected service evaluation level data.

The study has the goal to provide relevant data for clinical practice and management of patients with COPD to improve quality of care, and potentially prognosis, considering a more accurate characterisation of the patient living with COPD.

### Aims

To assess whether frailty correlates with cardiovascular outcomes in patients diagnosed with COPD according to guidelines. The following research questions will be addressed:

How many cardiovascular events (including hospital admissions due to cardiovascular cause) at 12 and 24 months in COPD patients living with frailty *vs* non-frail COPD patients. Coronary artery disease (CAD), aortic disease, peripheral artery disease (PAD), cerebrovascular disease, deep vein thrombosis (DVT) and pulmonary embolism (PE), and arrhythmias were selected as cardiovascular events. The list of ICD-10 codes related to cardiovascular events of special interest for the study protocol is shown in **Table 1**.How many deaths due to cardiovascular cause at 12 and 24 months in COPD patients living with frailty vs non-frail COPD patients.How many deaths due to all-cause mortality at 12 and 24 months in COPD patients living with frailty *vs* non-frail COPD patients.How many deaths due to COPD at 12 and 24 months in COPD patients living with frailty *vs* non-frail COPD patients.Prevalence of frailty in COPD.

**Table 1 pone.0300945.t001:** 

	ICD-10 code
**Coronary artery disease (CAD)**	
Angina	**I20**
Acute Myocardial Infarction (AMI)	**I21**
Heart failure	**I50**
**Aortic disease**	
Aortic aneurysm	**I71.2**
Abdominal aneurysm	**I71.4**
**Peripheral artery disease (PAD)**	**I73**
**Cerebrovascular disease**	
Ischemic stroke	**I63**
Intracranial hemorrhage	**I62**
Cerebral aneurysm	**I67.1**
Transient ischaemic attack (TIA)	**G45**
**Deep vein thrombosis (DVT)**	**I80**
**Pulmonary embolism (PE)**	**I26**
**Other venous embolism and thrombosis**	**I82**

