**Arrhythmias**	
Atrial fibrillation and flutter	**I48**
Other cardiac arrhythmias	**I49**

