### Cardiovascular events

These will be defined as the following. Any ICD-10 code reported in **Table 1** or the following event recorded in the hospital notes at 1 and 2 years will be considered as a cardiovascular event.

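### Three rows of Table 1 (DVT, PAD, TIA) use whole ICD-10 categories wider than the disease named, and a code alone is enough to count as a primary-outcome event

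*Protocol article*

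**What the plan says.** The Aims section of the protocol article names the disease classes that count: coronary, aortic and peripheral artery disease, and then "cerebrovascular disease, deep vein thrombosis (DVT) and pulmonary embolism (PE), and arrhythmias were selected as cardiovascular events". It refers to Table 1 for the related ICD-10 codes.

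The Cardiovascular events section turns the table into a rule: "Any ICD-10 code reported in Table 1 or the following event recorded in the hospital notes at 1 and 2 years" counts as a cardiovascular event. The two routes are joined by *or*, so a listed code suffices without support from the notes. Under Primary outcome, the number of these events at 12 and 24 months is the primary outcome.

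The rows at issue in Table 1 are:

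- "Deep vein thrombosis (DVT) I80"
- "Peripheral artery disease (PAD) I73"
- "Transient ischaemic attack (TIA) G45"

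Each is a bare three-character category. Elsewhere the table goes to the fourth character, as in "Abdominal aneurysm I71.4", and also for aortic aneurysm (I71.2) and cerebral aneurysm (I67.1).

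**The concern.** A three-character ICD-10 category takes in every sub-code below it. Where the category is broader than the row label, the literal rule scores diagnoses that the Aims section did not select, and each adds one to the primary count. Because some rows are narrowed to a sub-code and others are not, a coder cannot assume that the label silently limits the code.

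If such events occur at the same rate in every frailty group, they pull the rate ratios towards 1 and cost power. The comparison of mildly frail with not frail patients is the one exposed, because it is planned with almost no reserve.

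**Working it through.** **1. Label against code.** The contents of the categories are those of the ICD-10 classification, which the protocol adopts as its event definition but does not reprint.

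| Row label | Code listed | Also inside the category | Selected in Aims? |
|---|---|---|---|
| Deep vein thrombosis | I80 | I80.0, superficial leg-vein phlebitis | No |
| Peripheral artery disease | I73 | I73.0, Raynaud's syndrome | No |
| Transient ischaemic attack | G45 | G45.4, transient global amnesia | No; the row names TIA only |

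A patient with one such code in the year scores 1 under the stated rule and 0 under the row label.

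**2. The plan's own sample size.** Inputs from Power and sample size: proportions with at least one event at 1 year of 0.40, 0.60 and 0.75; type-1 error 0.025 per comparison; power 80%; groups of 120:120:80. Sidedness is not stated; I take two-sided, without continuity correction.

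n per group = [z(0.9875)·√(2·p̄·(1−p̄)) + z(0.80)·√(p₁(1−p₁)+p₂(1−p₂))]² / (p₂−p₁)²

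With p₁ = 0.40, p₂ = 0.60, p̄ = 0.50: [2.241 × 0.7071 + 0.842 × 0.6928]² / 0.04 = 118 per group, against 120 planned. Power at 120 per group is 80.9%. For 0.40 versus 0.75 at 120:80 it is 99.8%. The plan's figure reproduces and is not itself in error.

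**3. Effect of non-target events (assumed rates).** Let f be the probability that a patient has at least one non-target event in a year, equal in all groups, independent of true events and additional to the planned proportions. Then p′ = 1 − (1−p)(1−f). For f = 5%: 1 − 0.60 × 0.95 = 0.430 and 1 − 0.40 × 0.95 = 0.620.

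For the rate ratio, a plain Poisson mean is λ = −ln(1−p), giving 0.511 and 0.916, to which −ln(1−f) is added.

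| f (assumed) | Not frail / mildly frail | n per group for 80% | Power at 120:120 | Rate ratio | Power, CFS 6–8 vs 1–3 |
|---|---|---|---|---|---|
| 0 | 0.400 / 0.600 | 118 | 80.9% | 1.79 | 99.8% |
| 1% | 0.406 / 0.604 | 120 | 80.0% | 1.78 | 99.8% |
| 2% | 0.412 / 0.608 | 123 | 79.1% | 1.76 | 99.7% |
| 5% | 0.430 / 0.620 | 131 | 76.4% | 1.72 | 99.6% |
| 10% | 0.460 / 0.640 | 144 | 71.6% | 1.66 | 99.2% |

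For scale, 1% is about 3 of 320 patients a year (320 × 0.01 = 3.2) and 10% is 32.

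**The case against.** **The category contents are not in the document.** True: from the article alone one sees only uneven coding depth. But the protocol makes ICD-10 codes its event definition, so what I80 covers is the meaning of the plan's own term, not a result borrowed from an outside study. This does not remove the point.

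**Finer definitions may exist elsewhere.** The case report form (S1 File) is not shown, and sites may read the disease label as limiting the code. That may reduce the practical effect. It does not change the rule as printed, under which a code suffices; any narrower definition elsewhere would have to be reconciled with it. The local check under Validation data (25% of fields in 10% of cases) would not catch this, since a correctly recorded I73.0 would pass.

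**The size is assumed.** This stands in full. No rate of non-target codes is given, and at 1% the 80% target is still met. The 40/60/75% may already refer to events as the rule defines them, in which case adding f counts them twice. The primary model is a zero-inflated Poisson; for the same proportion without events its mean is at least as large as the plain Poisson mean, so a given f is an equal or smaller share of events. The table is best read as an upper case for each f.

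**Stronger readings that the document does not support.** A reader might infer that I49 is also too wide because it takes in isolated premature beats. But that row is labelled "Other cardiac arrhythmias" and the Aims section selects arrhythmias without limit, so label and code agree; whether such events should weigh as much as an infarction is a different question. A reader might also infer that the wide codes create a false frailty effect, through more cannulas and inpatient ECGs in frail patients. Cannula phlebitis may be coded in another chapter and the ECG route depends on I49, so nothing in the document supports a gradient across frailty groups.

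**Conclusion.** The point holds for three rows. As printed, I80, I73 and G45 let diagnoses outside the selected classes count towards the primary outcome on the code alone, while other rows of the table show that sub-codes were available.

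The effect is a conditional risk, not a demonstrated bias. If non-target events are equally common in all groups and additional to the planned proportions, an assumed 1% to 10% of patients per year would take power for mildly frail versus not frail from 80.9% to between 80.0% and about 72%. The CFS 6–8 comparison is hardly touched. The true rate is unknown and probably small. The case for acting rests on the clarity of the primary endpoint and the low cost of correction, more than on the size of the loss.

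**What to change.** Before outcome data are analysed, do one of two things:

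- In Table 1, restrict the three rows to sub-codes that match their labels: exclude I80.0, I73.0 and G45.4, and count I80 codes for an unspecified or other site (such as I80.9 and I80.8) only if the notes state a deep-vein thrombosis. Conditional counting of the unspecified codes avoids losing real thromboses coded without a site.
- Or add a sentence to the Cardiovascular events section that a Table 1 code counts only when the notes confirm the disease named in its row.

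Leave I49 as it is. Timing matters because narrowing the list after outcomes are known would look driven by the data.

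Cost: a table edit or one sentence, with no extra patients or visits. Sites must record the fourth character or check the notes, and the event count may fall slightly.

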**Arrhythmias**	
Atrial fibrillation and flutter	**I48**
Other cardiac arrhythmias	**I49**

## Materials and methods

### Study summary

**Table 2** provides the summary of the study information.

**Table 2 pone.0300945.t002:** Study summary.

Study Title	Influence of frailty on cardiovascular events and mortality in patients with COPD
Study Design	Observational
Study Participants	COPD outpatients
Planned Size of Sample	320
Follow up duration	24 months
Planned Study Period	24 months
Research Question/Aim(s)	To assess frailty and number of cardiovascular events in adult patients with COPD in stable condition. To correlate frailty with long-term cardiovascular mortality, all-cause mortality, and mortality due to COPD in patients with COPD.
	The prevalence of frailty in COPD will also be measured.

### Study design and setting

Study design: Multicentre European observational study. The study follows the STROBE statement for reporting of cohort studies.

Study setting: Two university hospitals and one local health care service in Italy, and university hospital site in the UK that provide care and follow up/scheduled visits for outpatients diagnosed with COPD will participate. The central study team subsequently provided the ethical approval, protocol, central organisation and long-term delivery of the project.

### Study population

#### Patient screening

Patients will be screened for inclusion criteria by the local team in the outpatient setting at each hospital site. The diagnosis of COPD will be according to the GOLD guidelines (www.goldcopd.org) and confirmed by a post-bronchodilator FEV_1_/FVC < 0.70.

Principal Investigators (PIs) at each site will have local responsibility for data quality and entry. Data collection will be carried out using the case report form (CRF) presented in the S1 File. Where personal information is collected at each site, it will be kept secure, and maintained. This will involve the creation of a number code for each patient (Patient Identification, PID) that will guarantee data anonymisation.

#### Inclusion criteria

Patients with age ≥40 years, with diagnosis of COPD of at least 1 year, in stable condition, without acute exacerbation in the last 30 days and/or all-cause hospitalisation in the last month, able to provide their written informed consent, will be included. Patients with concurrent diagnosis of asthma (asthma/COPD overlap syndrome) and alpha-1 antitrypsin deficiency are will also be included.

#### Exclusion criteria

Terminally ill patients, patients with concurrent diagnosis of interstitial lung disease, presence of restrictive pattern on spirometry, no history of smoking habit, not able to provide their written informed consent, will be excluded.

### Power and sample size

Assuming the proportion of those that are not frail (40%), mildly frail (60%) and moderately to severely frail (75%) will exhibit at least one cardiovascular event at 1 year. In order to detect these two comparisons (not frail, versus mildly frail & not frail versus moderately frail), using a chi-squared test with type-1 error = 0.025 and 80% power. We will need a minimum of 320 patients, approximately 120:120:80 for CFS 1–3, 4–5, 6–8 respectively.

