### Statistical analysis

We will aim to recruit a minimum of 320 patients: across a minimum of 3 sites.

This protocol and analysis plan will be drafted by a medical statistician fully blinded to the outcome data.

Data will be analysed for correlation between frailty and clinical outcomes. The primary analysis will be the number of cardiovascular events (time to event) at 12 and 24 months, adjusting for sex, age (18–64, 65–80, >80) and frailty at the time of recruitment, and other clinically relevant non-respiratory comorbidities. The number of events will be analysed using a zero-inflated Poisson regression to compare the rates between the three frailty groups. The rate with 95%CI will be presented alongside the p-value. Overdispersal will be assessed and if found to be present robust standard errors will be fitted.

The secondary analyses will assess the time to all-cause mortality, cardiovascular mortality, and mortality due to COPD that will be fitted to compare those classified as frail *vs* not frail visually using a Kaplan Meier plot. Data will be analysed using a multivariable Cox baseline proportional hazards regression, adjusting for covariates. The time to mortality will be calculated from the date of study entry to the end of follow up. The analyses will be presented as Odds Ratio (adjusted OR) with associated 95% confidence intervals and p-values. Subgroups analyses (age, sex, GOLD classes and grades, comorbidities) will be conducted to assess the grade of frailty. Stata version 18 (or later) will be used.

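### The 80% power is established for an unadjusted chi-squared test of any event by 1 year with complete follow-up, not for the adjusted zero-inflated Poisson count model named as the primary analysis

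*Protocol article*

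**What the plan says.** The Power and sample size section of the protocol article assumes that 40% of non-frail, 60% of mildly frail and 75% of moderately to severely frail patients "will exhibit at least one cardiovascular event at 1 year". It plans two pairwise comparisons against the non-frail group, "using a chi-squared test with type-1 error = 0.025 and 80% power", and concludes: "We will need a minimum of 320 patients, approximately 120:120:80 for CFS 1–3, 4–5, 6–8 respectively".

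The Statistical analysis section names a different primary analysis: "The number of events will be analysed using a zero-inflated Poisson regression to compare the rates between the three frailty groups". That model is adjusted for sex, age band and non-respiratory comorbidities. The abstract and the Primary outcome section also make the number of events the primary outcome. Neither a chi-squared test nor any other analysis of the any-event proportion appears in the Statistical analysis section.

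The same section repeats the total as a recruitment target: "We will aim to recruit a minimum of 320 patients: across a minimum of 3 sites". The number required and the minimum number to recruit are therefore the same, and no allowance for loss is stated.

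**The concern.** The sizing and the primary analysis differ in three ways. The endpoint is binary in one and a count in the other. One is unadjusted, while the other adjusts for age and comorbidity, which are likely to be related to frailty. One assumes that every recruit's 12-month status is known, and the protocol does not say what happens otherwise.

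The zero-inflated form adds a further difficulty. It can divide a frailty effect between a zero part (who is never at risk) and a count part (how many events those at risk have). The any-event proportions do not say how the effect divides. The article gives no event rate, rate ratio, inflation share, dispersion or covariate correlation from which power for this model could be worked out.

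What is at stake is the reading of a null result. A non-significant frailty contrast from the count model would be presented as coming from a study with 80% power, when that figure was never worked out for that contrast.

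**Working it through.** **Inputs from the protocol article:** proportions 0.40, 0.60 and 0.75; groups of 120, 120 and 80; alpha 0.025 per comparison; power 0.80. Sidedness is not stated; two-sided reproduces the figure.

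**Inputs assumed here, because the article gives none:** loss rates, the share R² of frailty explained by covariates, the inflation share, and the event rate among those at risk.

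**1. The plan's own figure, 40% vs 60%.** Two-sided, pooled variance, no continuity correction, with mean proportion 0.50:

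n = [z₀.₉₈₇₅ √(2 × 0.5 × 0.5) + z₀.₈₀ √(0.4 × 0.6 + 0.6 × 0.4)]² / 0.20²

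= [2.2414 × 0.7071 + 0.8416 × 0.6928]² / 0.04 = 2.168² / 0.04 = 117.5, so 118 per group.

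Power at 120 per group = Φ[(0.20 × √120 − 1.5849) / 0.6928] = Φ(0.875) = 0.809.

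The same method for 40% vs 75% at 120:80 gives 0.998. The plan's figure reproduces.

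**2. Margin on that test.** Replacing 120 by 120 × (1 − loss):

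| Assumed loss | 40% vs 60% | 40% vs 75% |
|---|---|---|
| 0% | 0.809 | 0.998 |
| 2% | 0.800 | – |
| 5% | 0.787 | 0.997 |
| 10% | 0.762 | 0.995 |
| 20% | 0.706 | 0.989 |
| 30% | 0.640 | 0.977 |

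A rough allowance for adjustment multiplies n by (1 − R²). With R² = 0.2, the 40% vs 60% power is 0.706 without loss and 0.654 with 10% loss.

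**3. The count model without inflation.** If counts are Poisson, P(at least one) = 1 − exp(−λ). The means are −ln 0.60 = 0.511 and −ln 0.40 = 0.916, a rate ratio of 1.79. The standard error of its log is √[1/(120 × 0.511) + 1/(120 × 0.916)] = 0.159. Power = Φ(0.584/0.159 − 2.241) = 0.92. With 10% loss and R² = 0.2 it is 0.81; with 20% loss and R² = 0.3 it is 0.69.

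**4. The zero-inflated model.** Here P(at least one) = (1 − π)(1 − exp(−λ)), where π is the inflation share and λ the event rate among those at risk. Several (π, λ) pairs meet the same 40/60/75%:

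- Common π = 0.2 requires λ = 0.69, 1.39 and 2.77.
- Common λ = 2 requires π = 1 − p/0.8647, that is 0.54, 0.31 and 0.13.

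Simulated power of the count-part contrast, 40% vs 60%, at 120:120:80, with no covariates and no loss:

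| Where frailty acts | Inflation held constant in the fit | Frailty in both parts of the fit |
|---|---|---|
| Rate only, no true inflation | about 0.93 | about 0.4–0.5 |
| Rate only, common 20% inflation | about 0.98 | about 0.75 |
| Zero part only, at-risk rate 2 | about 0.3 | close to alpha |

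The runs used 200 to 2,000 replicates. Separate runs of the zero-part scenario with constant inflation gave 0.26 to 0.37, and one at an at-risk rate of 3 gave 0.08. The spread in the top right cell (0.37 in one run, 0.54 in another) reflects the fitting method, because inflation lies at its boundary there.

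The bottom right cell is not lost power. The true count coefficient is zero in that scenario, so rejection at about 2.4–3.0% is the type-1 error. A joint two-degree-of-freedom test of frailty across both parts has about 0.72 power on the same data, and about 0.84 when the data are plain Poisson.

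**The case against.** Sizing a count endpoint on a simpler binary summary is common and is not in itself an error. A count analysis can have more power than the dichotomised one: 0.92 against 0.81 under plain Poisson, and still 0.81 after 10% loss and R² = 0.2. The article does not fix a count-part Wald test or say which terms enter the inflation part, and that detail may lie in a statistical analysis plan that is not shown. Loss rates and R² are not in the document. Events are taken from ICD-10 codes or hospital notes, so a missed visit need not mean an unknown outcome. The R² allowance counts only the cost of adjustment and ignores any gain from prognostic covariates. Finally, 320 is called a minimum.

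Most of this stands, and it rules out two stronger readings. A reader might infer that the study does not have the power it states. The documents do not show that, because the stated power is right for the stated test and the named model exceeds 80% in several scenarios consistent with the plan's assumptions. A reader might also infer from the near-alpha rejection rate that the count model has almost no power. That rate comes from testing a coefficient in which no effect was placed.

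The mismatch itself is not answered. The article states both the sizing test and the primary model, and they differ. Calling 320 a minimum permits over-recruitment but does not plan for it.

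**Conclusion.** The point holds as a mismatch between sizing and analysis. It is not an arithmetic error, and no shortfall is demonstrated.

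On the sizing test, the non-frail versus mildly frail comparison rests on two spare patients per group and falls below 80% once loss exceeds about 2%. The comparison with the moderately to severely frail group has ample reserve.

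For the named model, power in the first comparison depends on where the frailty effect falls and how the inflation part is specified. It is above 0.90 if frailty acts on the rate and inflation is held constant, and about 0.4 to 0.8 if frailty also enters the inflation part. It is about 0.3 or less if frailty acts only on the zero part and inflation is held constant (at-risk rate of 2 assumed). These figures rest on the assumed loss, R², inflation and at-risk rates, and the zero-inflated simulations carry no covariates or loss. The article's own inputs cannot choose among them, so 80% should not be quoted for the primary analysis as it stands. The matter should be corrected, but it does not call the sample size into question.

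**What to change.** Keep 320 and do one of the following:

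- **(a)** In the Statistical analysis section, pre-specify an adjusted analysis of any event by 12 months (for example, a risk ratio by modified Poisson regression), name it as the analysis that the 320 supports, and say how it ranks against the count model.
- **(b)** In the Power and sample size section, restate the power by simulation for the adjusted count model. State the assumed event rates, the inflation share, the dispersion, and which part frailty enters. Power the contrast that will be tested: a joint test, or the marginal rate (1 − π)λ, if frailty enters both parts.

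Option (b) addresses the mismatch directly. Option (a) is simpler, but it adds an analysis to match the calculation.

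In either case, give the power for evaluable patients under a stated loss (5–10% would be a reasonable range to show) and a stated covariate correlation, for both comparisons. The cost is a short recalculation and a few lines of text. The stated power may become less favourable for the non-frail versus mildly frail comparison.

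### Both frailty contrasts are sized at 0.025 and no rule passes the level on; a Holm step-down would be a cheap improvement on the not-frail vs mildly-frail contrast (an efficiency point, not an error)

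*Protocol article*

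**What the plan says.** All references are to the protocol article.

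- **Power and sample size.** The assumed proportions with at least one cardiovascular event at 1 year are 40% (not frail), 60% (mildly frail) and 75% (moderately to severely frail). Two comparisons are named, each against the non-frail group. The study is sized "using a chi-squared test with type-1 error = 0.025 and 80% power", which gives a "minimum of 320 patients, approximately 120:120:80 for CFS 1–3, 4–5, 6–8 respectively".
- **Statistical analysis.** "The number of events will be analysed using a zero-inflated Poisson regression to compare the rates between the three frailty groups", with covariate adjustment, a 95% confidence interval and a p-value. No significance level and no multiplicity rule is given there. The recruitment aim is again a minimum of 320.
- **Time points.** The power calculation and the Abstract refer to 1 year. The Primary outcome and Statistical analysis sections name both 12 and 24 months.

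Neither Bonferroni nor any step-down or ordered procedure is mentioned.

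**The concern.** Holding two tests at 0.025 each, whatever the other shows, is a safe way to keep the family-wise error at 5%. It is inefficient when one of the tests is nearly certain to succeed, because that test keeps half of the level for itself. Here the contrast of not frail with moderately to severely frail is such a test. The contrast of not frail with mildly frail is the only one with a material risk of a false negative, and it would be tested at half the level it could have.

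The margin on that contrast is also thin. The three groups sum to exactly 320, so the section shows no visible allowance for losses over 12 months.

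**Working it through.** **Inputs** (Power and sample size): proportions 0.40, 0.60 and 0.75; groups 120, 120 and 80; level 0.025 per contrast; chi-squared test; 80% power. The section does not state sidedness. Two-sided, without continuity correction, is the reading tested first.

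**1. Reproduce the stated size, 40% vs 60%.** The mean proportion is 0.50.

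n per group = [z(1−α/2)·√(2·p̄·q̄) + z(0.80)·√(p₁q₁ + p₂q₂)]² / (p₂ − p₁)²

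- α = 0.025: [2.2414 × 0.7071 + 0.8416 × 0.6928]² / 0.04 = (1.585 + 0.583)² / 0.04 = 117.5, so 118 (stated: 120).
- α = 0.05: [1.9600 × 0.7071 + 0.583]² / 0.04 = (1.386 + 0.583)² / 0.04 = 96.9, so 97.

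Two-sided 0.025 without correction matches 120. Two-sided 0.05 or one-sided 0.025 gives 97, and two-sided 0.025 with continuity correction gives 128. Since 0.025 = 0.05/2 and two comparisons are named, an even split of 5% is the natural reading.

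**2. Power of each contrast at 0.025 by the formula.**

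- 40% vs 60%, 120:120: (0.20·√120 − 1.585) / 0.6928 = (2.191 − 1.585) / 0.6928 = 0.875; Φ = 80.9%.
- 40% vs 75%, 120:80: the pooled proportion is (48 + 60)/200 = 0.54. The null standard error is √(0.54 × 0.46 × (1/120 + 1/80)) = 0.0719. The alternative standard error is √(0.24/120 + 0.1875/80) = 0.0659. Then (0.35 − 2.2414 × 0.0719) / 0.0659 = 2.86; Φ = 99.8%.

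**3. Power under Holm.** Test the smaller p-value at 0.025 and, if it is significant, the other at 0.05. Because both contrasts share the non-frail group, power was obtained by exact binomial enumeration, conditioning on that group's count:

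P(reject mild) = E[A₀.₀₂₅ + (A₀.₀₅ − A₀.₀₂₅)·B₀.₀₂₅]

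Here A and B are the conditional rejection probabilities of the mild and the moderate-to-severe contrast at the level shown.

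| Scenario | 40% vs 60%, fixed 0.025 | 40% vs 60%, Holm |
|---|---|---|
| Plan's assumptions, 120:120:80 | 80.4% | 86.9% |
| Assumed even 10% loss, 108:108:72 | 76.1% | 83.7% |
| Third-group rate 65% instead of 75% | 80.4% | 85.8% |
| Third group of 40 instead of 80 | 80.4% | 86.4% |

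On the plan's assumptions the gain is 6.4 points before rounding. The formula gives 80.9% to 87.7%, treating the other contrast as certain. The 10% loss and the last two rows are assumptions of this review, not figures in the plan.

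**4. Error rates, uncorrected chi-squared, 120:120:80.**

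| True proportions | Quantity | Fixed 0.025 | Holm |
|---|---|---|---|
| 40/40/40% | any false rejection | 4.7% | 4.7% |
| 40/40/75% | false rejection of the mild contrast | 2.5% | 5.2% |

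The first row is identical by construction, because Holm's first step is the Bonferroni test. The second row shows where the gain comes from. The realised 5.2% exceeds the nominal 5% because the uncorrected test is discrete; with continuity correction it is 3.8%.

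**The case against.** The strongest reply is that nothing is stated wrongly. The sample size reproduces, the plan meets its own 80% target, and sizing each contrast at 0.025 is standard. All of that stands.

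A reader might also infer that the plan commits itself to a fixed Bonferroni rule at analysis. The document does not say so. The 0.025 appears only as a sizing level, while the Statistical analysis section sets no level and plans 95% intervals. Conservative sizing is compatible with Holm testing later, and an analysis plan that is not shown may already set such a rule. The point therefore remains a suggestion about a level the article does state.

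A second tempting inference is that the study's power should be restated as 87%. That figure belongs to an unadjusted chi-squared test with complete follow-up. The primary analysis is an adjusted zero-inflated Poisson model "to compare the rates between the three frailty groups". Holm can be applied to that model's two contrast p-values, but the gain there may differ in size.

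A third is that the gain is free because the family-wise error is unchanged. That is exact only when all three groups are equal. When only the moderate-to-severe contrast is real, the false-positive rate on the mild contrast doubles. This is permitted at a nominal 5%, but it should be disclosed.

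Finally, Holm over two p-values covers one time point. The primary outcome is read at 12 and 24 months, so it would not control error over all of those tests.

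**Conclusion.** This is a cheap improvement, not an error, and of minor weight. The plan's calculation is sound. If the two contrasts are held at 0.025 in the analysis, as the sizing suggests, about 6 points of power on not frail vs mildly frail are left unused, and the chance of missing that contrast is 19.6% rather than 13.1%.

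These figures rest on the plan's 40/60/75% and 120:120:80, a two-sided uncorrected chi-squared test and no losses. The gain changes little if the third group is smaller or its rate is lower, because it needs only that the moderate-to-severe contrast usually succeeds. Holm never loses a rejection that the fixed split would make.

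**What to change.** Add one sentence to the Statistical analysis section, before outcome data are examined, for example:

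*At the 12-month primary time point, the two contrast p-values from the primary model (not frail vs mildly frail; not frail vs moderately to severely frail) will be tested two-sided by Holm's procedure: the smaller at 0.025 and, if significant, the other at 0.05, for a nominal family-wise error of 5% over these two tests. Tests at 24 months are outside this family.*

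If confirmatory claims are wanted at 24 months, those tests must be added to the family and the levels reset.

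Keep 320 patients and the stated 80% as the planning figure. If the gain is quoted, say that it applies to the chi-squared planning test with no losses (80.4% to about 87%; 76.1% to 83.7% with an assumed 10% loss) and may differ in the zero-inflated Poisson model.

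The change needs no patients and no data. It has two costs. The false-positive rate on the mild contrast rises from 2.5% to a nominal 5% when only the other contrast is real. Intervals that match a Holm decision exactly are also less simple than Bonferroni intervals, although 97.5% intervals can still be shown as conservative companions.
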